#### Family or Social Network Level

At the family or social network level, the core Hispanic values of *familismo* and *collectivismo* will be leveraged to promote CGM uptake. Two components of the individual-level intervention will integrate (1) family members (or friends) and (2) a peer educator. A family member will coattend in-person CGM educational sessions (see Individual Level section) with each participant with T1D to provide support in acquiring CGM knowledge and skills and their application in real-world settings.

Previous studies reveal that education alone in Hispanic adults with diabetes is insufficient, and peer support may be warranted for successful behavior change [24,51,53,69-72]. Led by a Hispanic bilingual, bicultural peer with T1D, the virtual support group sessions will provide unique support [73]. Research suggests that the peer format will foster the Hispanic cultural value of *collectivismo* to promote participant self-disclosure and valuing of opinions, particularly as they pertain to CGM [58]. Moreover, the common bond created through the shared lived experience of T1D and initiating or using CGM, a bond not frequently shared between patients and their providers, will likewise promote support in CGM adoption. The Hispanic bilingual, bicultural peer received 10 hours of Diabetes Community Care Coordinator training from the Association of Diabetes Care and Education Specialists in preparation for delivering the virtual support group sessions [73].

#### Health Care Provider Level

Intervention providers (doctors of medicine [MDs], doctors of osteopathic medicine [DO], and advanced practice registered nurses [APRNs]) received intensive clinical support for T1D care in preparation for the study. We developed and deployed 2 Project ECHO programs to strengthen intervention provider knowledge and skills with a 4-week program in T1D insulin therapy and an 8-week program of Hispanic culturally sensitive CGM education and care (Table 3). Health care providers will see intervention participants at baseline, 3 months, and 6 months or more frequently as indicated (Figure 3).

**Table 3 table3:** Project ECHO (Extension for Community Healthcare Outcomes) insulin and continuous glucose monitoring (CGM) content.

Week			Project ECHO topics
**Insulin therapy**			
	Week 1	T1D^a^ and review of insulins	
	Week 2	Selection of insulins-patient factors	
	Week 3	Dosing insulin	
	Week 4	Adjusting basal or bolus insulin doses	
**CGM education and care**			
	Week 1	CGM basics in Hispanic adults with T1D	
	Week 2	Using CGM to improve clinical outcomes in Hispanic adults with T1D	
	Week 3	Accessing CGM data	
	Week 4	Implementation of CGM in Hispanic adults with T1D	
	Week 5	CGM payor coverage and reimbursement	
	Week 6	Barriers and strategies to optimize CGM use in Hispanic adults with T1D	
	Week 7	Counseling Hispanic adults with T1D on using CGM	
	Week 8	Case studies	

^a^T1D: type 1 diabetes.

### Control Condition

The control condition consists of three components: (1) virtual telehealth visits, (2) support phone calls, and (3) self-monitoring of blood glucose (SMBG)–informed T1D insulin therapy (Figure 4).

**Figure 4 figure4:**
[figure not shown]
Control study timeline. CDCES: certified diabetes care and education specialist; SMBG: self-monitoring of blood glucose.

#### Virtual Telehealth Visits and Support Phone Calls

Four virtual telehealth visits will be delivered via the HIPAA-compliant Zoom meeting platform by a bilingual (English or Spanish) Hispanic CDCES (Figure 4). Session content focuses on increasing participant knowledge and skills related to SMBG. SMBG topics include T1D and blood glucose levels; blood glucose targets, measurement, and monitoring; and causes and management of hypoglycemia and hyperglycemia. American Diabetes Association and Centers for Disease Control educational materials, available in Spanish or English, will be used to guide each session. In addition, control participants will have 5 phone calls with the Hispanic CDCES (Figure 4). The goal of these phone calls is to reinforce SMBG testing knowledge and skills.

#### T1D Insulin Therapy

Control providers (MDs, DOs, and APRNs) participated in an in-depth, 4-week ECHO program on T1D insulin therapy (Table 3). Control site providers will manage insulin therapy for participants informed by respective HbA_1c_ levels and SMBG data. Control site providers will see participants at baseline, 3 months, and 6 months or more frequently if clinically warranted (Figure 4).

### Measures and Data Management

Data will be collected at baseline, weekly, 3 months, and 6 months. Data will be entered into a REDCap (Research Electronic Data Capture; Vanderbilt University) [74,75] database by trained data collectors who are fluent in English and Spanish (Table 4 and Textbox 1).

**Table 4 table4:** Background and outcome measures.

			Baseline		Weekly		3 months		6 months
**Demographics**									
	Age	✓							
	Income	✓							
	Education	✓							
	Gender	✓							
	Language preference	✓							
	Nativity	✓							
	Time living in the United States	✓							
**Health-related factors**									
	Year of T1D^a^ diagnosis	✓							
	Primary insurance	✓							
	Chronic diabetes complications	✓							
	Number of hypoglycemic-related ED^b^ visits over the past 3 months	✓				✓		✓	
	Number of hypoglycemic-related hospitalizations over the past 3 months	✓				✓		✓	
	Number of hyperglycemic-related ED visits over the past 3 months	✓				✓		✓	
	Number of hyperglycemic-related hospitalizations over the past 3 months	✓				✓		✓	
**Glucose control**									
	HbA_1c_^c^	✓				✓		✓	
**Depression**									
	Patient Health Questionnaire	✓				✓		✓	
**Quality of life**							✓		✓
	Medical Outcomes Survey Short Form-36	✓				✓		✓	
**Social support**									
	Perceived Social Support from Family Scale	✓				✓		✓	
**Patient-provider trust**									
	Interpersonal Processes of Care Survey: Short-Form	✓				✓		✓	
**CGM^d^ metrics (intervention participants only)**									
	Glucose time in range					✓		✓	
	Glucose time below range					✓		✓	
	Glucose time above range					✓		✓	
**SDOH^e^ factors**									
	PRAPARE^f^	✓							
	Transportation to 4 weekly CDCES^g^ in-person visits (study month 1)			✓					

^a^T1D: type 1 diabetes.

^b^ED: emergency department.

^c^HbA_1c_: glycated hemoglobin.

^d^CGM: continuous glucose monitoring.

^e^SDOH: social determinants of health.

^f^PRAPARE: Protocol for Responding to & Assessing Patients’ Assets, Risks & Experiences.

^g^CDCES: certified diabetes care and education specialist.

Selected PRAPARE (Protocol for Responding to & Assessing Patients’ Assets, Risks & Experiences) items.At any point in the past 2 years, has season or migrant farm work been your or your family’s main source of income?Nominal level of measurementHave you been discharged from the armed forces of the United States?Nominal level of measurementWhat is your housing situation today?Nominal level of measurementAre you worried about losing your housing?Nominal level of measurementWhat is your current work situation?Ordinal level of measurementIn the past year, have you or any family members you live with been unable to get any of the following when it was really needed? (Food and utilities, clothing, childcare, medicine or any health care, and phone)Nominal level of measurement, respectivelyHas a lack of transportation kept you from medical appointments, meetings, work, or getting things needed for daily living?Nominal level of measurementHow often do you see or talk to people who you care about and feel close to? (For example, talking to friends on the phone, visiting friends or family, going to church, or club meetings)Ordinal level of measurementAre you a refugee?Nominal level of measurement

#### Background Factors

Demographics, health-related factors, and SDOH will be measured (Table 4). At baseline, demographic (eg, nativity, race, ethnicity, and language preference) and health-related (ie, duration of T1D and specific diabetes chronic complications) data will be collected. SDOH will be measured at baseline and weekly. At baseline, SDOH will be measured with PRAPARE (Protocol for Responding to & Assessing Patients’ Assets, Risks & Experiences). The nationally standardized PRAPARE, developed by the National Association of Community Health Centers, is routinely used at the study FQHC to support social needs screening in its primary care settings. PRAPARE is a 21-item, unsummed measure available in English and Spanish. It will be administered at baseline with data capture of selected items (items 3-8, 11, 14-16, 19; Textbox 1) [76]. Upon identifying a social risk, the CDCES, as indicated, will refer participants, for example, to 211 Connecticut. Accessible by phone or online, 211 Connecticut provides referrals to a wide range of health and human service resources, including transportation, basic needs, housing, and food, among several others. Additional SDOH data (eg, participant transportation to study visits) will be collected weekly for each of the CDCES educational sessions (Textbox 1).

#### Primary Outcome: Feasibility

In this study, feasibility will be assessed in terms of (1) recruitment and enrollment, (2) retention, (3) adherence, (4) study procedures and implementation, and (5) acceptability (Textbox 2).

Feasibility and acceptability measures.
**Recruitment and enrollment**
Number screened per monthNumber enrolled per monthProportion of eligible screens enrolledReason for study refusalRecruitment yield by type
**Retention**
Retention rate by intervention or control groupRetention differential rates by participant characteristicsProportion of completed data collection points
**Adherence**
Continuous glucose monitoring use (number of days worn, % time active)Intervention and control schedule (% followed)
**Study procedures or implementation**
Data collection fidelityCertified diabetes care and education specialist (CDCES) intervention fidelityPeer-led support group fidelityIntervention and control doses
**Acceptability**
Intervention acceptability (CDCES, peer, and providers, respectively) by focus group interviews

During screening visits, demographic characteristics will be entered into our REDCap recruitment and enrollment database. The recruitment and enrollment database will track recruitment sources, eligibility screening, and enrollment outcomes. Qualitative data on the rationale for study refusal will also be captured in the database. The database will be used to inform modifications to our recruitment strategies to optimize our yield of enrolled participants. In addition, the recruitment and enrollment database will be linked to a retention database. The retention database will track retention yields, retention by differential rates by participant characteristics, and the proportion of completed data by groups (intervention or control).

The REDCap database will be used to track adherence to the intervention and control schedules (Figures 3 and 4). For intervention participants, data on the number of days the CGM was worn and the percentage of time the CGM was active will be collected from the electronic health record (EHR), specifically an electronic copy of the CGM report after each provider visit at 3 and 6 months.

Using the REDCap database, participant intervention and control doses will also be tracked. The number of provider visits completed (3 planned study visits and additional visits as indicated) will be tracked over the 6-month study period. For all participants, the completed number and duration of CDCES and peer-led intervention or control components will be recorded.

Addressing the fidelity of study procedures, data collectors received 6 hours of training in using REDCap in preparation for the RCT. Following training, direct observation revealed that data collectors had achieved high competency in related skills acquisition. During the RCT, fidelity of data collection will be assessed by self-report. Prior to completing a REDCap module for a participant, the database requires that related data entry be endorsed as verified, completed, or incomplete. In addition, in REDCap, open-ended data will be entered on any problems encountered with data collection at baseline, 3 months, and 6 months for each study participant.

With respect to intervention fidelity, specifically the 4 weekly CGM educational sessions, we will use self-report and in vivo observation assessments. A fidelity checklist was developed and integrated into the FQHC’s EHR for each of the 4 sessions, respectively. Using the EHR, the CDCES will have a dedicated template for each of the 4 sessions, corresponding with the goals and content for each session, as displayed in Table 2. The templates have structured domains for entry of quantitative data (achievement of specific session goals and delivery of planned content or not) and corresponding qualitative data, such as participant motivation and goals for CGM, among others. The CDCES will self-report achievement of specific session goals and delivery of planned content or not by using a parallel checklist embedded in each of the session templates. Further, the CDCES will be randomly observed for adherence and competence in delivering the intervention protocol using a fidelity measure designed for this study.

Fidelity of the virtual support group sessions will be assessed by self-report using a web-based data fidelity system. For each of the 7 support group sessions, respectively, the web-based system will capture quantitative and qualitative data. The peer educator, for each session, will be prompted to endorse yes or no regarding the achievement of session goals and delivery of planned content in addition to entering parallel open-ended data.

Acceptability will be assessed with focus group interviews (FGIs) to be held with intervention participants, providers, and CDCES, respectively. FGI interview guides will pose questions on aspects of study processes or procedures (eg, recruitment, retention, data collection, intervention content, frequency of contact, duration of contact, and interventionist delivery).

#### Secondary Outcomes

Physiological outcomes are HbA_1c_, time in range, time below range, time above range, and frequency of hypoglycemic- or hyperglycemic-related ED visits or hospitalizations (Textbox 1). HbA_1c_ will be measured with the DCA 2000 point-of-care analyzer with a capillary blood sample, the standard measure of HbA_1c_ determination at the study FQHC. CGM glycemic metrics will be captured from FreeStyle Libre View reports (intervention participants only). The frequency of hypoglycemic- or hyperglycemic-related ED visits or hospitalizations over the past 3 months will be based on participant self-report (Textbox 1).

Psychosocial outcomes are depression, quality of life (QOL), social support, and interpersonal processes of care. All psychosocial measures are available in English and Spanish. Depression will be assessed with the 2-item Patient Health Questionnaire (PHQ) and 9-item PHQ. The PHQ-2 is a screening tool for depression. The PHQ-2, using the first 2 items of the PHQ-9, inquires about depressed mood and anhedonia over the past 2 weeks with item scores ranging from 0=not at all to 3=nearly every day. A total PHQ-2 score of >3 suggests major depressive disorder and warrants administration of the PHQ-9 [77]. PHQ-9 item scores likewise range from 0 to 3 (maximum score of 27). A threshold score of >10 indicates mild major depression, >15 or higher indicates moderate major depression, and >20 indicates severe major depression [78].

QOL will be measured by the Medical Outcomes Survey Short Form-36. This well-validated and reliable measure has 8 sections to capture distinct domains of QOL. Each section yields a scored scale, which is a weighted sum of the items in each section. Pooled scores are calculated to generate a total score, ranging from 0 to 100, with lower and higher scores indicating less or greater health-related QOL, respectively (Textbox 1) [77-79].

Social support will be assessed with the Multidimensional Scale of Perceived Social Support (MSPSS). The 12-item MSPSS assesses the perceived adequacy of support from family, friends, and significant others with corresponding subscales. The MSPSS is presented in a 7-point Likert-type format. Response options range from 1=very strongly disagree to 7=very strongly agree, with higher scores revealing greater levels of perceived social support. MSPSS subscale and total scale scores are computed with a specified formula. The MSPSS has demonstrated validity and reliability in Hispanic populations [80,81].

The Interpersonal Processes of Care Survey Short Form measures doctor communication, decision-making, and interpersonal style over the past 12 months. The 18-item Short Form was modified for this study to assess provider (MD, DO, and APRN) communication over the past 3 months. The Interpersonal Processes of Care Survey Short Form has 7 subscales presented in a 5-point Likert-type format; response choices range from 1=never to 7=always. The 3 communication subscales measure lack of clarity (2 items), elicit concerns and responses (3 items), and explain results (2 items). The decision-making subscale assesses patient-centered decision-making (1 item), while 3 interpersonal style subscales measure emotional support and compassion (3 items), discrimination due to race or ethnicity (2 items), and disrespectful office staff (3 items). For each subscale, item responses are averaged with a range of 1-5, with higher scores indicating greater levels [82].

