## Methods

### Study Design and Sampling

A mixed methods, pragmatic pilot RCT will be used to evaluate the study’s aims. Mixed methods will be used to assess study feasibility and acceptability, while quantitative methods will be used to assess RCT outcomes.

We randomized 4 Connecticut FQHC sites to serve as control (n=2) or intervention (n=2) sites. Inclusion and exclusion criteria are listed in Table 1. We plan to enroll 15 intervention and 15 control participants. Our sampling goal reflects that the RCT is primarily focused on the assessment of feasibility rather than intervention efficacy, as there is a lack of CGM intervention studies for Hispanic adults with T1D at FQHC. Therefore, the pilot study will test key aspects of the study design, such as recruitment strategies, data collection methods, intervention protocols, and participant engagement, before conducting a full-scale RCT. The total sample size of 30 will support the estimation of the proportions of participants who have “satisfactory” feasibility measures with SEs that cannot exceed ±0.1. Additionally, the “per group” sample sizes (15 a piece) will support the estimation of variances for outcome variables with sufficient precision to guide power analyses for a subsequent, full-scale RCT.

**Table 1 table1:** Inclusion and exclusion criteria.

			Potentially eligible intervention participants		Potentially eligible control participants

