**Exclusion criteria**					
	Pregnant or planning to become pregnant	✓		✓	
	Lactating	✓		✓	
	Serious illness that may prevent study participation (eg, severe depression, advanced cancer, and advanced dementia)^a^	✓		✓	
	<6 months life expectancy^a^	✓		✓	
	Uncorrected hearing impairment^a^	✓		✓	
	Uncorrected vision impairment^a^	✓		✓	
	Alcohol or drug abuse or dependency^a^	✓		✓	

^a^Prescreening criteria.

^b^T1D: type 1 diabetes.

^c^FQHC: federally qualified health center.

^d^PCP: primary care provider.

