To quantify intervention signals, we will begin by contrasting HbA_1c_ levels between the intervention and control participants. To do this, we will apply linear mixed modeling (LMM) using study arm assignment (intervention vs control) and time (3 and 6 months) as “main effects,” the corresponding baseline value of HbA_1c_ as a covariate, and FQHC site variable as well as the “participant” identifier as random effects. This approach will support statistical testing of intervention effects on the mean value of HbA_1c_ while controlling for differences in baseline levels of the variable, accounting for clustering effects with study sites, and adjusting for correlations within participants over time. After using this strategy to assess the main effect of the intervention on the mean value of HbA_1c_, we will investigate the possibility of “intervention-by-time” and “intervention-by-site” interactions and the possibility that any imbalances in baseline participant characteristics (sociodemographic variables and health history factors) between study groups might confound valid estimation of intervention effects. Because the RCT is primarily concerned with feasibility assessment and will involve small samples with limited statistical power, the focus of these analyses will be “effect estimation” rather than formal statistical testing. In the second stage of analysis, we will apply the same modeling strategy to contrast the other physiological outcomes and the psychosocial measures between the intervention and control participants.

Throughout our analyses using LMM, we will attempt to respond to evidence of nonnormality in any of the outcome measures by applying normalizing transformations. If no transformation achieves approximate normality (as is likely to be the case for the time in range, below range, and above range variables as well as the counts of hypo- and hyperglycemic clinical events), we will, instead, apply a generalized linear mixed model with a link function appropriate to the distribution of the outcome measure. Mixed models of repeated measures are robust to the effects of missing observations that occur “at random.” Depending on the extent of missing data (while acknowledging restrictions imposed by the study’s small sample size), sensitivity analyses based on multiple imputations may be conducted to evaluate the potential impact of nonrandom missing data on estimates of the intervention effects.

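### If the PHQ-9 total is the modelled depression score, giving it only after a PHQ-2 total above 3 leaves a sparse, outcome-selected contrast; collect all nine items from everyone or name the PHQ-2 as the analysed score

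*Protocol article*

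**What the plan says.** The Secondary Outcomes section of the protocol article lists depression among the psychosocial outcomes and names two forms: "Depression will be assessed with the 2-item Patient Health Questionnaire (PHQ) and 9-item PHQ". It then gives them different roles. Of the shorter form it says "The PHQ-2 is a screening tool for depression", and of the longer one, "A total PHQ-2 score of >3 suggests major depressive disorder and warrants administration of the PHQ-9". Table 4 schedules the Patient Health Questionnaire at baseline, 3 months and 6 months in a single row that does not separate the two forms.

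In the Data Analytic Plan, Study Aim 2 sets out a linear mixed model for HbA1c with arm and time (3 and 6 months) as main effects and the baseline value as covariate. The same strategy is then used to "contrast the other physiological outcomes and the psychosocial measures between the intervention and control participants". The plan also takes standardized effect sizes, variance estimates and correlations across the three time points from these models, for each psychosocial outcome, to help design the full-scale trial.

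Table 1 excludes "Serious illness that may prevent study participation (eg, severe depression, advanced cancer, and advanced dementia" and similar conditions. Nothing in the article states what share of participants is expected to score above 3 on the PHQ-2, or which PHQ score is analysed.

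**The concern.** A screen-then-test sequence is a sensible clinical workflow but a poor way to collect a repeated outcome. If the PHQ-9 total is the outcome, two of its own nine items decide whether it is observed. At baseline this removes the covariate, and so the participant, for anyone at or below the cut-off. At follow-up it removes the score of anyone who has improved to 3 or below, a response that occurs after randomisation and that the intervention may influence.

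What would be at stake is the use the pilot makes of the number. The effect size, variance and temporal correlation for the PHQ-9 would come from a few people selected for staying symptomatic, and they would be carried into the planning of the full-scale trial.

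**Working it through.** **The article's own figure.** The only sample-size figure is "feasibility measures with SEs that cannot exceed ±0.1" for N = 30. The largest standard error of a proportion is sqrt(0.25/30) = 0.0913, below 0.1, so it reproduces. It concerns feasibility proportions and does not bear on the PHQ question.

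**What the cut-off does to the score.** Each item is scored 0 to 3, so a PHQ-2 total above 3 means 4, 5 or 6. The other seven items add 0 to 21. Any recorded PHQ-9 total therefore lies between 4 and 27. A participant at or below the cut-off could have a total anywhere from 0 to 3 + 21 = 24, and none of these totals is recorded.

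**How many have a baseline PHQ-9.** Let p be the share with PHQ-2 above 3. The documents do not give p, so it is assumed and varied. The expected number is 30 × p. The chance that fewer than half of the 30 have a baseline PHQ-9 is the binomial probability of 14 or fewer.

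| Assumed p | Expected of 30 | Per arm of 15 | P(fewer than 15 of 30) |
|---|---|---|---|
| 0.1 | 3 | 1.5 | 1.00 |
| 0.2 | 6 | 3 | 1.00 |
| 0.3 | 9 | 4.5 | 0.98 |
| 0.4 | 12 | 6 | 0.83 |
| 0.5 | 15 | 7.5 | 0.43 |
| 0.6 | 18 | 9 | 0.10 |

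**How many have a usable pair.** The model needs the baseline score and at least one follow-up score. Take one follow-up visit with the same share p above the cut-off. If the same people stay above it, the expected number of pairs is 30 × p. If status at the two visits is unrelated, it is 30 × p². For p = 0.1, 0.2 and 0.3 the brackets are 0.3 to 3, 1.2 to 6 and 2.7 to 9. These are expected counts before dropout.

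**Direction of the bias.** An illustrative simulation used 200,000 participants per setting, nine 0–3 items driven by one latent trait, a baseline-to-follow-up latent correlation of 0.6 and a benefit of 0.5 latent SD. Follow-up PHQ-9 was adjusted for baseline PHQ-9. All parameters are assumptions.

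| Share above 3 at baseline | Pairs expected of 30 | Arm effect, all participants | Arm effect, above 3 at both visits | Shrinkage |
|---|---|---|---|---|
| 0.15 | 1.3 | -2.66 | -1.80 | 1 - 1.80/2.66 = 32% |
| 0.28 | 3.3 | -3.27 | -1.67 | 1 - 1.67/3.27 = 49% |
| 0.49 | 8.0 | -3.68 | -1.66 | 1 - 1.66/3.68 = 55% |
| 0.66 | 13.3 | -3.53 | -1.60 | 1 - 1.60/3.53 = 55% |

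Among those above the cut-off at baseline, the mean PHQ-9 change was about -0.8 in those still measured at follow-up and -9.4 to -9.8 in those no longer measured. A different set of assumptions (9% to 16% above the cut-off at baseline, latent correlation 0.7, the same 0.5 SD benefit) gave shrinkage of 7% to 25%. The direction is the same in every setting; the size depends on the assumptions.

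**The case against.** The strongest reply is that the depression outcome is not missing. The PHQ-2 is planned for every participant at all three visits, it is named as a depression measure, and it still records people who recover. This stands. A reader might infer that the depression outcome as a whole is missing by design, but the documents support that only for the PHQ-9, and only if its total is what is modelled.

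Three other tempting readings also go too far. That most participants would lack a PHQ-9 is plausible but has no figure behind it, and it becomes doubtful once about half score above 3. The severe-depression exclusion leans toward lower shares, but it covers only illness that may prevent participation. That the gap falls exactly on those who improve is wrong: people never above the cut-off are also unmeasured, and people who improve but stay above 3 are still measured. Nor is the expected count at a given p a ceiling on how many score above the cut-off.

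The article also does not say outright that the PHQ-9 is withheld at or below the cut-off. That is inferred from the screening role and the trigger sentence. It is the natural reading, because a screener has little purpose if everyone takes the second test.

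It can further be said that missingness fixed by an observed PHQ-2 may be at random given the PHQ-2, and that multiple imputation is foreseen as a possible sensitivity analysis. In principle that is right. But the stated model does not include the PHQ-2, the baseline covariate is missing as well as the outcome, and no PHQ-9 total is ever observed at or below the cut-off, so imputation would be extrapolation from very few records.

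Finally, the choice of analysed score may sit in a full protocol or analysis plan that is not shown. That choice can indeed be made there. The collection rule cannot be repaired there, because no analysis plan recovers items that were never asked.

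**Conclusion.** The concern holds in conditional form. As the article reads, the PHQ-9 follows from a PHQ-2 total above 3. If the PHQ-9 total is put through the Study Aim 2 model, the comparison rests on those above the cut-off at baseline and again at follow-up, and it is pulled toward no effect. The expected number with a baseline score is 3, 6 or 9 of 30 at assumed shares of 10%, 20% or 30%, with fewer pairs. The simulated shrinkage illustrates direction only and is not an estimate for this trial. If the PHQ-2 total is modelled instead, the problem does not arise.

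The weight is moderate. Depression is one of several secondary outcomes in a feasibility pilot that aims at effect estimation and calls its planning statistics less than definitive. It is still worth acting on, because those statistics are meant for the full-scale trial and the loss occurs at data collection.

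**What to change.** For research scoring, administer all nine PHQ items to every participant at baseline, 3 and 6 months, and name the PHQ-9 total as the modelled depression outcome. The PHQ-2 total is still obtained from the first two items, so any screening use of it is unaffected. The cost is seven extra short items per visit for participants who would otherwise stop after two.

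If the two-step procedure is kept, state that the PHQ-2 total is the modelled depression outcome, and report the PHQ-9 descriptively only, without an arm contrast, effect size, variance or temporal correlation for planning. This is a wording change; its price is a shorter scale, 0 to 6 instead of 0 to 27.

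The article reports the first enrolment in May 2024. For any participant whose baseline visit has already passed without the PHQ-9, only the second option gives a complete series.
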